## Unblinding

2.4

Throughout the investigation, individuals will be closely observed throughout the investigation. Should any participant experience serious adverse reactions related to rTMS, such as dizziness, headache, nausea, vomiting, tinnitus, arrhythmia, or seizures, immediate unblinding will be performed to minimize potential bias.

## Study interventions

2.5

All rTMS procedures were performed by professionally trained and experienced operators who had undergone standardized training prior to study initiation. The rTMS intervention is administered on the day before surgery and the day of surgery, resulting in two sessions per participant. This protocol is designed to accommodate the limited perioperative time window while providing a rapid, clinically feasible intervention.

Stimulation parameters are based on established neurophysiological principles. The right dorsolateral prefrontal cortex (DLPFC) is selected as the target region due to its role in negative emotional processing and its involvement in anxiety-related neural circuits. Low-frequency (1 Hz) stimulation is applied to reduce cortical excitability and modulate prefrontal–limbic pathways. The entire procedure strictly followed a unified protocol to ensure consistency in coil positioning, stimulation parameters, and patient interaction.

First, a circular coil was used to locate the stimulation target. The primary motor cortex (M1) was clinically identified as the area 2 cm anterior and 1–1.5 cm lateral to the intersection of the naso-occipital line and the temporoparietal line on the patient’s scalp (i.e., the Cz point). The resting motor threshold (RMT) for each patient was then determined as a reference for setting the stimulation intensity, expressed as a percentage of the rTMS device’s maximum output (24). The RMT was defined, using the visual observation technique, as the lowest stimulation intensity capable of eliciting a visible contraction in the target muscle in 5 out of 10 trials while the muscle was completely relaxed (24). Subsequently, a figure-8 coil was used to target the right DLPFC. The center of the coil was positioned parallel to the patient’s scalp, with its midpoint aligned directly over the stimulation site. The rTMS treatment was then delivered at an intensity of 80–120% of the RMT using a low frequency of 1 Hz (21). Both groups will undergo the intervention using identical devices and operational procedures. However, in the sham rTMS group, the device will not deliver pulsed magnetic fields to the brain but will only produce similar audible clicking sounds and scalp sensations/vibrations mimicking those emitted during active stimulation.

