## Randomization and blinding

2.3

This study utilizes a block randomization method. A computer-generated random block sequence of 4 or 6 will be used to centrally randomize participants into either the active rTMS group or the sham rTMS group at a 1:1 ratio. The randomization sequence was generated by an independent researcher from the study team using a computer-based program. This researcher had no involvement in participant recruitment, intervention delivery, outcome assessment, or data analysis. Sequentially numbered, opaque, sealed envelopes were used to ensure allocation concealment. After enrollment and baseline assessment, the envelope was opened by the operator responsible for administering the rTMS at the time of the first rTMS session to determine group assignment. To ensure effective blinding, both groups will use identical stimulation equipment and follow the same operating procedures. However, the device used in the sham rTMS group will not deliver pulsed magnetic fields to the brain; it will only produce sounds and vibrations similar to those generated during actual pulse stimulation. Throughout the study, all other parties, including the participants, outcome assessors, and data analysts, will remain blinded to group assignment.

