This study specifically focuses on the female patient population. Epidemiological evidence indicates that the prevalence of anxiety disorders is consistently higher in females than in males (5, 6). During the perioperative period, female patient’s exhibit heightened sensitivity to surgical stress due to a combination of hormonal fluctuations and psychosocial factors, resulting in more pronounced anxiety compared to their male counterparts (8, 17). Therefore, concentrating the study population on females helps control for gender as a potential confounding variable, enhances the homogeneity of the research findings, and provides more targeted evidence for the future development of precision perioperative anxiety management protocols specifically for female patients. To ensure the reproducibility and scientific rigor of the intervention, this protocol provides a clear definition of the rTMS parameters. Based on established rTMS treatment guidelines and relevant clinical studies, low-frequency (1 Hz) stimulation targeting the right dorsolateral prefrontal cortex (DLPFC) was selected as the intervention protocol (40, 41). This stimulation paradigm has been shown to effectively modulate DLPFC excitability, thereby downregulating hyperactivity in subcortical regions such as the amygdala via the prefrontal-limbic pathway, ultimately alleviating anxiety symptoms (39, 42). Accordingly, this single-center, prospective, randomized, sham-controlled study aims to evaluate the effect of rTMS on perioperative anxiety in female patients.

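### As written, the resting motor threshold appears to be set with a circular coil but applied to a figure-8 treatment coil, so 80–120% of RMT need not be 80–120% of the treatment-coil threshold

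*Protocol article*

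**What the plan says.** Section 2.5 (Study interventions) of the protocol article sets out the procedure in sequence:

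1. "First, a circular coil was used to locate the stimulation target".
2. The primary motor cortex is identified from scalp landmarks.
3. "The resting motor threshold (RMT) for each patient was then determined as a reference for setting the stimulation intensity", and it is "expressed as a percentage of the rTMS device’s maximum output". The RMT is defined "as the lowest stimulation intensity capable of eliciting a visible contraction in the target muscle in 5 out of 10 trials", with the muscle relaxed. Neither sentence names a coil.
4. "Subsequently, a figure-8 coil was used to target the right DLPFC".
5. "The rTMS treatment was then delivered at an intensity of 80–120% of the RMT", at 1 Hz.

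The circular coil is the only coil mentioned up to and including the RMT step. Nothing says that the threshold is measured again with the figure-8 coil or that the setting is converted between coils. Section 2.3 states that "both groups will use identical stimulation equipment and follow the same operating procedures". The Discussion says that "this protocol provides a clear definition of the rTMS parameters".

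**The concern.** The RMT is the only reference by which intensity is adapted to the individual patient. It is recorded as a stimulator setting, not as a field at the cortex. Two coils of different geometry on the same stimulator need not induce the same cortical field at the same setting, so a threshold found with one coil does not fix the same relative dose on the other. An operator who follows section 2.5 literally would find the threshold with the circular coil and treat with the figure-8 coil.

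Two things are at stake. Active participants may be treated below or above the intended share of their own threshold on the treatment coil; if below, a null result would be harder to separate from under-dosing. The reported intensity would also not be comparable with that of studies that set the RMT on the treatment coil.

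**Working it through.** **Which coil measures the RMT?** The text does not say outright, so this is a reading of the order of steps. The circular coil comes first. The target located at that stage can only sensibly be the motor cortex, because the next sentence identifies the motor cortex and the DLPFC is reached later with the other coil. The RMT follows, with no change of coil mentioned, and the figure-8 coil enters after it. The natural reading is a circular-coil RMT. It remains an inference.

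**Inputs.** From section 2.5: a treatment range of 80–120% of RMT, and an RMT expressed as a percentage of maximum device output. The range is a prescribed setting, so there is no calculation in the plan to reproduce. The documents give no threshold for either coil.

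**Formula.** Let *k* be the RMT with the circular coil divided by the RMT with the figure-8 coil, both as a percentage of device output. If threshold corresponds to a given effective field, *k* is also the figure-8 coil's effective cortical field per 1% of output relative to the circular coil's. Then:

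intensity as % of treatment-coil RMT = nominal % × *k*

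**Break-even values from the protocol's own limits.**
- The whole window is below treatment-coil threshold when 120 × *k* < 100, i.e. *k* < 100/120 = 0.833.
- The whole window is at or above threshold when 80 × *k* ≥ 100, i.e. *k* ≥ 100/80 = 1.25.

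**Illustrations.** Every *k* here is assumed; none comes from the documents.

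| Assumed *k* | 80 × *k* | 120 × *k* | Range as % of treatment-coil RMT |
|---|---|---|---|
| 0.8 | 64 | 96 | 64–96 |
| 0.9 | 72 | 108 | 72–108 |
| 1.0 | 80 | 120 | 80–120 |
| 1.1 | 88 | 132 | 88–132 |
| 1.25 | 100 | 150 | 100–150 |

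The stated range equals the range on the treatment coil only when *k* = 1. Any shift would concern the active arm, planned at 126 participants (section 2.10).

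**What does not change.** The sample size inputs in section 2.10 (difference 1.3, SD 2.9, alpha 0.05, power 0.80) do not involve intensity. Section 2.3 gives both arms the same equipment and procedure, so the between-group comparison is not biased by the choice of coil.

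**The case against.** The strongest reply is that the defect is inferred. The only task the text gives the circular coil is locating the target; thresholding is not assigned to it, and a journal article may leave the thresholding coil to an operating manual. Section 2.5 also refers to a uniform procedure and trained operators, and cites sources for the RMT method and the intensity that are not at hand. It is true that the coil is not named. But the point is not an omitted detail: the article names both coils and states an order, and an operator following that order would use different coils for threshold and treatment.

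A second reply is that the coil dependence of a percentage-of-output threshold is not stated in the documents, and that nothing in them shows these two coils to differ. The first half is general physics and does not need a source. The second half stands, which is why no size or direction is claimed.

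A third reply is that a 40-point window already allows intensities below or above threshold, so a modest shift adds little. It is fair that the width of the range makes a null result hard to interpret in any case. A coil mismatch, however, moves both ends of the window, and a wide range does not correct for that.

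Finally, the Discussion's claim of clear parameters goes on to frequency and target, not intensity. That contrast is weak, and the point does not rest on it.

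**Conclusion.** The point holds in its limited form: the sequence in section 2.5 implies a circular-coil RMT applied to a figure-8 coil, so the stated 80–120% is not tied to threshold on the coil that delivers treatment. This rests on two premises: that the RMT is taken with the coil in use at that step, and that the two coils differ in field per unit of output. The size is unknown and may be zero. The consequence is confined to the definition, delivery and reporting of the active dose; there is no effect on the validity of the randomised comparison, the error rate or the sample size calculation. It is an inexpensive improvement, not a serious flaw, and confidence is medium because the coil used for the RMT is inferred.

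**What to change.** State in section 2.5 that the RMT is determined with the same figure-8 coil and stimulator that deliver treatment, in both arms, and put the same instruction in the operators' procedure.

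- If the figure-8 coil is already used for the RMT, only the order of the sentences needs correcting.
- For any participant already dosed from a circular-coil RMT, report intensity as a percentage of circular-coil RMT.
- The choice of percentage remains with the sponsor.

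The cost is one sentence and an operator instruction. The figure-8 coil is already part of every session, so no extra visit, staff, device or change of analysis is needed. The one drawback is that finding the threshold with a more focal coil may take a few minutes longer.

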## Anesthesia

2.6

Standard intraoperative monitoring is initiated upon patient arrival in the operating room [e.g., pulse oximetry, electrocardiogram (ECG), non-invasive blood pressure (NIBP), and bispectral index (BIS)].

General anesthesia is induced with 2.0–2.5 mg·kg^−1^ propofol, 0.3–0.5 μg·kg^−1^ sufentanil, and 0.6–1 mg·kg^−1^ rocuronium. Tracheal intubation is performed once BIS falls below 60, and mechanical ventilation is utilized to keep end-expiratory CO₂ between 35 and 45 mmHg. Anesthesia is continued with intravenous propofol (4–6 mg·kg^−1^·h^−1^), remifentanil (0.1–0.3 μg·kg^−1^·min^−1^), and 1% sevoflurane inhalation to keep BIS between 40 and 60. Vasoactive agents are administered as required to keep hemodynamic stability.

Postoperatively, patients are transferred to the post-anesthesia (PACU) or surgical intensive (SICU) care units, and extubation occurs upon recovery of consciousness. Analgesia is provided via patient-controlled intravenous analgesia (PCIA) using 100 μg sufentanil and 8 mg ondansetron diluted to 100 mL with normal saline, with a background infusion of 1.5–2.0 mL·h^−1^ and patient-controlled bolus doses of 1.0–2.0 mL.

## Outcomes

2.7

### Primary outcome

2.7.1

The primary outcome is the change in anxiety score from baseline to 3 days post-operation, measured using the HADS-A (25), with a score of ≥8 indicating clinically significant anxiety (26). The minimal clinically important difference (MCID) for the Hospital Anxiety and Depression Scale (HADS) is not fixed and varies across clinical contexts and analytical methods. Evidence from anchor-based studies and systematic reviews suggests that a change of approximately 1.5–2.0 points in the HADS total or subscale scores is generally considered clinically meaningful (27–29). Anxiety was assessed preoperatively in the ward on the day pre-operation (T0) prior to the first rTMS intervention, and the second intervention was administered in the pre-operative holding area on the day of operation. Postoperative anxiety scores were measured on days 1 (T1), 2 (T2), 3 (T3), and the 3rd month post-operation (T4).

### Secondary outcomes

2.7.2

Secondary outcomes comprise: anxiety scores (T1–T4); occurrence of post-operative delirium [evaluated via the Confusion Assessment Technique for the ICU (30) during T1–T3]; pain scores [10-point Numeric Rating Scale (NRS) (31) during T1–T3, 0 = no pain, 10 = worst imaginable pain]; frailty scores [FRAIL Index (32) during T1–T4, 0 = most robust, 5 = most frail]; and sleep quality [Pittsburgh Sleep Quality Index (PSQI) (33) during T1–T4, 0–21, higher scores denote poorer sleep].

## Adverse events and safety

2.8

All participants will undergo rigorous pre-enrollment screening to minimize potential risks associated with rTMS. Individuals with a history of epilepsy, major neurological disorders, or intracranial metal implants will be excluded. During each stimulation session, participants will be closely monitored for adverse symptoms (e.g., dizziness, headache, nausea, vomiting, tinnitus, arrhythmia, or seizures) (34). To ensure participant safety, an independent monitoring team was designated to oversee the study conduct, data quality, and adverse events. All adverse events are systematically recorded and reported to the principal investigator and the institutional ethics committee. The ethics committee retains the authority to recommend modification or termination of the study if necessary. Continuous safety monitoring is implemented throughout the study period, and predefined criteria for study discontinuation include the occurrence of serious adverse events or any unexpected safety concerns.

## Data collection and management

2.9

After each participant visit, data will be recorded on paper Case Report Forms (CRFs) and subsequently entered into Microsoft Excel by an investigator not involved in the intervention. All study data will be securely stored in a separate, restricted-access location. The principal investigator will regularly review all adverse events and, when necessary, convene investigator meetings to evaluate the study’s risk–benefit profile. Unblinding procedures may be implemented if required to ensure participant safety and protect their legal rights. An independent data monitoring team will oversee the accumulated safety and efficacy data to determine whether the study should continue.

## Sample size

2.10

We conducted a pilot study comparing active versus sham rTMS in female patients. The pilot results showed a mean difference in anxiety scores of 1.3 between groups, with a standard deviation (SD) of 2.9. Depending on a significance level of 0.05 and a power of 0.80, we calculated a sample size of 78 patients/group via PASS 15.0. Accounting for a 10% dropout rate and pre-specified subgroup analyses, we aimed to recruit 126 participants/group to confirm sufficient study reliability.

## Statistical analysis

2.11

All analyses will be conducted according to the intention-to-treat (ITT) principle, with participants assessed in their originally assigned groups regardless of protocol adherence or treatment received. Baseline demographic and clinical characteristics will be summarized to evaluate balance between the groups. Continuous variables will be assessed for normality using the Shapiro–Wilk test. Normally distributed variables will be presented as mean ± standard deviation (SD) and compared using independent t-tests, while non-normally distributed variables will be expressed as median (interquartile range, IQR) and analyzed using the Mann–Whitney U test. Categorical variables will be expressed as counts and percentages and compared using the chi-square test or Fisher’s exact test.

The primary outcome will be analyzed using a linear mixed-effects model, including treatment group, time, and treatment-by-time interaction as fixed effects, and a random intercept for each subject to account for within-subject correlations. Baseline HADS-A score, age, type of surgery, and relevant perioperative variables (e.g., anesthesia duration) will be included as covariates to control for potential confounding.

Secondary outcomes will be assessed via a linear mixed-effects model, comprising baseline values as covariates. Fixed effects will involve treatment, time, and the treatment-by-time interaction, with a random intercept for subjects accounting for within-subject variability. The treatment-by-time interaction will be initially examined. If significant, group differences and within-group changes at each time point will be assessed, with Bonferroni correction applied for multiple comparisons of baseline changes in anxiety scores. If not significant, only the major effect of treatment will be evaluated, and no Bonferroni correction will be utilized for time-specific treatment effects. Binary outcomes will be compared via the *χ*^2^ test or Fisher’s exact test, with relative risk (RR) and 95% confidence intervals (CI) reported.

In the exploratory analyses, to investigate the heterogeneity of rTMS effects across subgroups within the anxious population, we performed a series of subgroup analyses for the primary outcome measure. The primary subgroup analysis was depending on the level of patient anxiety: individuals with a HADS-A score ≥8 were defined as having anxiety symptoms, with scores of 8–10 (mild), 11–14 (moderate), and 15–21 (severe). We also examined subgroup effects according to surgery type, PSQI score (≤15 vs. > 15), and FRAIL scale result (no frailty vs. pre-frailty or frailty). These analyses were conducted by adding an interaction term between the treatment group and the subgroup variable to the linear mixed-effects model for the primary outcome. Effect heterogeneity was examined by estimating the importance of interaction terms. The adjusted odds ratio (aOR) and its 95% CI for each subgroup were displayed in a forest plot.

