### Study design

2.1

This randomized controlled study will be conducted at The Affiliated Hospital of Jiaxing University. Participant recruitment is scheduled to begin on March 2, 2025. A total of 252 female patients undergoing elective surgery will be enrolled and randomly assigned in a 1:1 ratio to either the active rTMS group or the sham rTMS group. Ethical approval for the study was granted by the hospital’s Ethics Committee (Approval No. 2025-KY-049) on February 12, 2025. The trial was registered with the Chinese Clinical Trial Registry on February 14, 2025 (Registration No. ChiCTR2500097991). The schedule for enrollment, interventions, and assessments is presented in Table 1, and study design is illustrated in the flowchart (Figure 1).

**Table 1 tab1:** Study timeline.

Timepoint	Study period					
	On the day pre-operation	on the day of operation	T1	T2	T3	T4
Enrolment						
Inclusion criteria	**×**					
Exclusion criteria	**×**					
Informed consent	**×**					
Randomization	**×**					
Allocation						
Interventions						
Active rTMS group	**×**	**×**				
Sham rTMS group	**×**	**×**				
Outcome measurement						
HADS-A	**×**		**×**	**×**	**×**	**×**
NRS			**×**	**×**	**×**	
POD			**×**	**×**	**×**	
FRAIL			**×**	**×**	**×**	**×**
PSQI			**×**	**×**	**×**	**×**

PSQI, Pittsburgh Sleep Quality Index; NRS, Numeric Rating Scale; POD, postoperative delirium; rTMS, repetitive transcranial magnetic stimulation; FRAIL, Fatigue, Resistance, Ambulation, Illness and Loss of Weight Index; T1, the 1st day post-operation; HADS-A, Hospital Anxiety and Depression Scale-Anxiety subscale; T2, the 2nd day post-operation; T3, the 3rd day post-operation; T4, the 3rd month post-operation.

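### A random intercept alone implies one variance and one correlation across days 1–3 and month 3, so the day-3 standard error and the treatment-by-time test can be modestly miscalibrated

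*Protocol article*

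**What the plan says.** Protocol article, section 2.11 (Statistical analysis): the primary outcome gets a linear mixed model with treatment, time and their interaction, several covariates including baseline HADS-A, and "a random intercept for each subject to account for within-subject correlations". The secondary outcomes get the same kind of model, "with a random intercept for subjects accounting for within-subject variability". Neither paragraph mentions a residual covariance structure, visit-specific variances, a random slope or robust standard errors.

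Section 2.7.1 (Primary outcome) defines the endpoint as the HADS-A change from baseline to day 3 and adds: "Postoperative anxiety scores were measured on days 1 (T1), 2 (T2), 3 (T3), and the 3rd month post-operation (T4"). Section 2.7.2 lists anxiety, FRAIL and PSQI over T1–T4, and NRS pain over T1–T3 only.

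The secondary-outcomes paragraph of 2.11 uses the interaction as a gate. If it is significant, the visits are compared one by one. If not, only the overall treatment effect is assessed. Section 2.11 does not list the visits that enter the primary model.

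**The concern.** A single random intercept with independent, equal-variance residuals is compound symmetry. Every visit has the same variance, and every pair of visits has the same correlation. That would require day 2 to relate to day 3 exactly as it relates to a visit three months later, and scores to be as variable in the ward as at month 3.

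Two inferences rest on this. The day-3 contrast takes its standard error from the variance averaged over visits, not from the day-3 variance, so visits outside the primary endpoint influence the primary confidence interval. The interaction test relies on equal correlation, and it decides which comparisons follow.

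**Working it through.** **Inputs from the article.** Section 2.10: "mean difference in anxiety scores of 1.3 between groups", "with a standard deviation (SD) of 2.9", alpha 0.05 and power 0.80, 126 recruited per group, 10% dropout. Section 2.1: 1:1 allocation. Two-sided testing is assumed.

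**Step 1: the stated sample size.** The plan reports "a power of 0.80, we calculated a sample size of 78 patients/group via PASS 15.0". The normal formula gives n = 2(1.960 + 0.842)² × 2.9² / 1.3² = 78.1. A t-test version gives 79.1, and power at 78 per group is 0.799. The figure is reproduced.

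**Step 2: the day-3 standard error.** With complete data the estimate is the plain difference in day-3 means.
- True SE = √(2 × day-3 variance / n). With SD 2.9 and n = 126 this is √(2 × 8.41 / 126) = 0.365.
- Model SE = √(2 × average visit variance / n).
- Ratio = √(average variance / day-3 variance), and type I error = 2[1 − Φ(1.96 × ratio)].

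Correlations do not appear in the ratio. Only unequal variances move it.

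The article gives one SD and no visit-specific values. The visit SDs below are therefore assumptions, with day 3 held at 2.9. The interaction column assumes correlations of 0.7 (adjacent days), 0.6 (days 1 and 3) and 0.3 (any day with month 3), except in the first row, where all are 0.6.

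| SDs at T1, T2, T3, T4 | Average variance | SE ratio | Day-3 type I error | Interaction type I error |
|---|---|---|---|---|
| 2.9 throughout, all correlations 0.6 | 8.41 | 1.000 | 0.050 | 0.050 |
| 2.9 throughout | 8.41 | 1.000 | 0.050 | 0.061 |
| 2.9, 2.9, 2.9, 3.5 | 9.37 | 1.056 | 0.039 | 0.067 |
| 2.9, 2.9, 2.9, 4.0 | 10.31 | 1.107 | 0.030 | 0.071 |
| 2.9, 2.9, 2.9, 2.3 | 7.63 | 0.952 | 0.062 | 0.057 |
| 2.0, 2.5, 2.9, 2.9 | 6.77 | 0.897 | 0.079 | 0.066 |

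Raising the day-to-day correlations to 0.8 and 0.7 with equal SDs takes the interaction figure to 0.071. In 20,000 simulated trials each, four of these rows gave (day 3 / interaction): 0.048 / 0.048 for the first, 0.050 / 0.059 for the second, 0.037 / 0.065 for month-3 SD 3.5, and 0.063 / 0.055 for month-3 SD 2.3.

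**Step 3: why the interaction test is affected.** In the second row the average correlation is (0.7 + 0.7 + 0.6 + 3 × 0.3)/6 = 0.483. The model gives every between-visit difference a variance of 2(1 − 0.483) = 1.03 in units of the visit variance. The true values are 0.6 for adjacent days, 0.8 for days 1 and 3, and 1.4 for any day against month 3. Differences involving month 3 are therefore judged against too small a variance.

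**Step 4: T1–T3 only.** The interaction error falls to 0.050–0.053. Day-3 error is 0.050 if the three SDs are equal. With SDs 2.0, 2.5, 2.9 the average variance is 6.22, the ratio 0.860 and the error 0.092. With 3.5, 3.2, 2.9 they are 10.30, 1.107 and 0.030.

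**Step 5: equal raw SDs are not a safeguard.** The model adjusts for baseline with one slope. Suppose equal SDs (set to 1) and baseline correlations of 0.6 on days 1–3 and 0.3 at month 3 (assumed). The common slope is (3 × 0.6 + 0.3)/4 = 0.525. The residual variance, 1 − 2 × 0.525 × ρ + 0.525², is 0.646 on each day and 0.961 at month 3, averaging 0.724. The ratio is √(0.724/0.646) = 1.059 and the day-3 error 0.038. With correlations 0.7, 0.6, 0.5, 0.3 the average is again 0.724, but day 3 has 0.751. The ratio is then 0.982 and the error 0.054.

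**Step 6: power.** For 1.3 points, power = Φ(1.3 / true SE − 1.96 × ratio). At 126 per group it is 0.945 with the correct SE and 0.92 to 0.97 across all scenarios in steps 2 and 4. At 113 per group (126 × 0.9) it is 0.92 with the correct SE and Φ(3.370 − 2.170) = 0.885 at the largest ratio, 1.107.

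**The case against.** The best reply is that a random intercept does not exclude a structured or heterogeneous residual matrix. Compound symmetry follows only when the default independent residuals are added, and a condensed article may leave such detail to an analysis plan. That is fair as to wording, and the conclusion is conditional on that default. It does not remove the point, because both model descriptions name the random intercept as the term that accounts for within-subject dependence. That is a stated choice.

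Other limits stand in full:
- A reader might infer that the primary standard error is miscalibrated as a matter of fact. The article gives no visit-specific SDs or correlations, so this is a risk of modest size and unknown sign.
- A reader might infer that unequal correlation distorts the day-3 standard error. With complete data it does not (second row of the table).
- Month 3 in the primary model is an inference. Section 2.7.1 lists T4 under the primary-outcome heading, but the endpoint stops at day 3. Without T4 the interaction problem nearly disappears, while the day-3 problem remains if the in-hospital SDs differ.
- The interaction gate stands in the secondary-outcomes paragraph. It refers to anxiety scores, but its use for the primary analysis is not stated.
- A treatment contrast of month 3 against day 1 would be affected more, but the plan does not list it as a test, so it is no measure of harm here.

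**Conclusion.** The point holds as a conditional one and should be acted on, though it does not endanger the trial. Given independent, equal-variance residuals, day-3 type I error is about 3% to 8% under the assumed SDs with T1–T4 modelled, and 3% to 9% with T1–T3 only. The sign depends on whether day 3 is less or more variable than the average visit. The treatment-by-time test runs at about 6% to 7% with month 3 included and close to 5% without it. This matters most for the secondary analyses of anxiety, FRAIL and PSQI, where T1–T4 and the gate are both stated. Power for the planned difference stays above 0.9 at 126 per group. All these sizes rest on assumed SDs and correlations and on complete data.

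**What to change.** In section 2.11:
- Name the visits that enter each model.
- Replace the random intercept with an unstructured within-subject covariance over the visits at which each score is measured: T1–T4 for HADS-A, FRAIL and PSQI, and T1–T3 for NRS pain. Fit by REML with Kenward-Roger degrees of freedom.
- Test the day-3 treatment contrast directly as the primary analysis, without the interaction gate.
- State the fallback if the model does not converge: heterogeneous Toeplitz first, then a random intercept with robust standard errors.

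The cost is a few sentences and some covariance parameters: 4 × 5 / 2 = 10 for four visits or 3 × 4 / 2 = 6 for three, against 2 for the random intercept. With about 250 patients these are easily estimated. The small chance of non-convergence is covered by the fallback. In return, the day-3 variance is estimated from its own visit, and the interaction test returns to its nominal level apart from small-sample error.
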